### 2.8. Sample Size Calculation

The sample size was calculated using G*Power software, version 3.1.9.2. Based on a previous study, our control group’s expected post-treatment PAS score is 4.62 ± 0.77 [48]. According to a power calculation of 80% and assuming a clinically relevant difference of one point on the PAS score between the study groups, with a standard deviation of 1.2 [49], we determined a total sample size of 55 participants. The calculation is based on an alpha level of 95%, accounting for a 15% dropout rate.

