### 2.9. Statistical Analysis

Data will be analyzed using the Statistical Package for the Social Sciences (SPSS) for Windows (version 26, IBM, Armonk, NY, USA). Categorical data will be reported as frequencies and percentages, while continuous variables will be summarized using means and standard deviations. The Shapiro–Wilk test will be used to assess data normality. Differences between groups will be examined with the Chi-square test for categorical variables. For continuous variables, Student’s t-test will be applied for normally distributed data, and the Mann–Whitney U test will be used for non-parametric data. Effect sizes will be calculated using Cohen’s d, with the following values: a small effect is indicated by 0.3, a moderate effect is indicated by 0.5, and a large effect is indicated by 0.8.

Statistical significance will be determined at *p* < 0.05. Participants with adherence rates of 80% or less, based on home diaries and attendance to standard speech and language sessions, will be excluded from the statistical analysis.

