## 3. Results

The expected outcomes include improved swallowing function. Patients are supposed to improve swallowing safety and efficiency. The addition of respiratory training to standard intervention is expected to improve coordination between breathing and swallowing, thereby reducing the risk of aspiration and facilitating better management of various food textures. A reduction in the frequency and severity of aspiration events is expected, leading to improved airway protection and a lower incidence of aspiration pneumonia. The respiratory training program is designed to strengthen both inspiratory and expiratory muscles. As a result, significant gains in respiratory muscle strength are expected, as evidenced by increased MIP and MEP values. Patients are also expected to achieve a more effective cough, which is relevant for clearing the airway and reducing the risk of aspiration pneumonia. This improvement should be reflected in higher peak cough flow measurements. Enhancements in swallowing ability are likely to contribute to a better quality of life, including reduced symptoms related to dysphagia and increased comfort during eating and drinking.

The home-based format of the program is expected to improve adherence, promote consistent participation, and achieve better long-term results. By integrating respiratory training with standard therapeutic interventions, the program aims to address both swallowing and respiratory issues more effectively, leading to improved overall rehabilitation outcomes.

The authors will present the study results in a peer-reviewed journal. The procedures and patient involvement at various stages of the study will be illustrated in a flow diagram. The article will highlight the main findings, starting with a table that details the descriptive characteristics of the sample. This will be followed by data comparing baseline outcomes between groups for both primary and secondary measures. Finally, the results of the intervention outcomes will be presented, including within-group and between-group changes, with effect sizes calculated using Cohen’s d.

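### Arms are compared by unadjusted two-sample tests although every outcome is measured at baseline, and the plan does not say whether the post score or the change is tested

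*Protocol article*

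**What the plan says.** Section 2.9 gives the whole between-group analysis of continuous variables in one sentence: "Student’s t-test will be applied for normally distributed data", with the Mann–Whitney U test otherwise. Neither that section nor any other mentions a baseline covariate, an analysis of covariance or a mixed model.

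Table 1 schedules aspiration risk, respiratory muscle strength, peak cough flow, oral intake and quality of life both before and after the intervention. Section 3 also plans to present "data comparing baseline outcomes between groups for both primary and secondary measures".

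On the quantity compared, three places bear on the question:
- Section 2.8 anchors the sizing on a post score: "our control group’s expected post-treatment PAS score is 4.62 ± 0.77". It then sizes the trial "assuming a clinically relevant difference of one point on the PAS score between the study groups", "with a standard deviation of 1.2", without saying whether that SD belongs to the post score or to the change.
- Section 3 describes the reporting as "including within-group and between-group changes, with effect sizes calculated using Cohen’s d".
- Section 2.9 does not say which of the two goes into the t-test or the Mann–Whitney test.

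**The concern.** A patient's baseline value usually predicts the follow-up value of the same measure. A two-sample test on the post score leaves that information unused. A test on the change uses it with a fixed weight of one, which adds noise when the pre-post correlation is low. Regression on baseline estimates the weight from the data. In a trial planned for about 46 completers, the difference in precision can matter.

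The open quantity is a second issue. The post-score and change comparisons estimate the same effect under randomisation, but with different precision, and in any one data set they can give different p-values. A primary analysis should fix one of them in advance.

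**Working it through.** **Inputs.** From Section 2.8: difference 1 PAS point, SD 1.2, power 80%, dropout 15%, total 55. Alpha is read as 0.05; two-sided is assumed because it reproduces the total. Section 2.5 gives 1:1 allocation. The pre-post correlation r is not in the document and is assumed at 0.3, 0.5 and 0.7. Baseline and post SDs are assumed equal.

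**Step 1: reproduce the plan's figure.** By the normal approximation, n per arm = 2 × (1.960 + 0.842)² × 1.2² / 1² = 22.6, so 23 per arm and 46 in total. Then 46 / 0.85 = 54.1, rounded up to 55, which matches. The sizing is therefore that of an unadjusted two-sample comparison and takes no credit for baseline. (The exact t calculation gives 24 per arm, and 48 / 0.85 = 56.5, so 57.)

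**Step 2: effective SD of each analysis**, taking 1.2 as the SD of the post score:
- post score: 1.2
- change: 1.2 × √(2(1 − r))
- baseline-adjusted: 1.2 × √(1 − r²)

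**Step 3: power by noncentral t, 23 per arm, difference 1.** The last column charges the adjusted analysis for its covariate: 43 instead of 44 degrees of freedom, and variance multiplied by 1 + 1/42 for expected chance imbalance.

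| r | SD of change | Adjusted SD | Post score | Change | Adjusted, no charge | Adjusted, charged |
|---|---|---|---|---|---|---|
| 0.3 | 1.42 | 1.14 | 78.9% | 64.7% | 82.6% | 81.6% |
| 0.5 | 1.20 | 1.04 | 78.9% | 78.9% | 89.1% | 88.3% |
| 0.7 | 0.93 | 0.86 | 78.9% | 94.6% | 97.2% | 96.9% |

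**Step 4: low correlations.** With the same charge, the adjusted analysis has 77.9% at r = 0, 78.3% at r = 0.1, 78.8% at r = 0.15 and 79.6% at r = 0.2, against 78.9% for the post score. It breaks even just above r = 0.15, and the worst case is a loss of about one point.

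**Step 5: the other reading of the SD.** If 1.2 is the SD of the change, the change test has 78.9%. The adjusted variance relative to change is (1 + r)/2, that is 0.65, 0.75 and 0.85. Charged power is then 92.3%, 88.3% and 84.2% at r = 0.3, 0.5 and 0.7. Adjustment still gains.

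**Step 6: effect of the open choice.** On the first reading, testing change instead of the post score moves power by 64.7 − 78.9 = −14.2 points at r = 0.3 and by 94.6 − 78.9 = +15.7 points at r = 0.7.

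**The case against.** The strongest reply is that nothing here is an error. The two-sample test is valid under 1:1 randomisation, and it is the test for which the trial was sized. That stands. A reader might infer that the unadjusted comparison is biased, that it mishandles chance baseline differences, or that a change score brings in regression to the mean. The documents do not support this. Chance imbalance is already covered by the type I error of the test, both comparisons are unbiased over randomisation, and regression to the mean is expected equally in both arms. Nor does 78.9% against the stated 80% show a wrong sample size: it is only the exact t against the normal approximation.

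The size of the gain rests on r, which the protocol does not give. That also stands. It would be tempting to say that adjustment wins at every correlation, but step 4 shows that it does not at about 0.15 or below.

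PAS is an 8-point ordinal scale and may well go to the Mann–Whitney test, which normal-theory power does not describe. The figures are therefore approximate for the outcome on which the trial was sized.

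Finally, Sections 2.8 and 3 do not strictly contradict each other: changes can be reported while post scores are tested. A separate analysis plan might name the quantity, so one cannot conclude that the choice will be made after the data are seen. What remains is that the article has a statistical section which selects the tests, leaves out the baseline and does not name what is tested. Such a plan could add adjustment only by departing from Section 2.9.

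**Conclusion.** The point holds as one of efficiency and specification, not of validity. Section 2.9 sets an unadjusted comparison although the baseline values are already collected, and it leaves open whether the post score or the change is tested. At 23 per arm, adjustment raises approximate power over the post-score test by about 3 points at r = 0.3 (81.6 − 78.9 = 2.7), 9 at r = 0.5 (88.3 − 78.9 = 9.4) and 18 at r = 0.7 (96.9 − 78.9 = 18.0). It exceeds the change-score test at each of these values, on either reading of the SD. These figures assume normal theory, equal SDs at both visits and a correlation that the protocol does not state. The change should be made, but the trial would remain interpretable without it.

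**What to change.** In Section 2.9, define the primary between-group analysis as the post-intervention value compared by arm, adjusted for the baseline value of the same outcome, and report the adjusted difference (or the model's effect measure) with a 95% confidence interval:
- MIP, MEP, peak cough flow and SWAL-QOL: linear ANCOVA.
- PAS and FOIS: a baseline-adjusted ordinal (proportional-odds) or rank-based model.

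This replaces the choice of test by Shapiro–Wilk for these comparisons. In Section 2.8, say whether the SD of 1.2 is for the post score or the change, and tie the sizing to the named quantity. The total of 55 need not change. In Section 3, present the adjusted between-group difference as the result and within-group changes descriptively only, and say how Cohen's d relates to the adjusted analysis.

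The cost is one degree of freedom, at most about one point of power if baseline predicts almost nothing, and some extra modelling work, mainly for the two ordinal scales. No further data, visits or patients are needed.

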### 2.6. Intervention Protocol

Patients allocated to the experimental group will participate in a 6-week home-based respiratory muscle training program in addition to the standard speech and language intervention. Patients in the control group will receive only the standard intervention. The protocol of both interventions is illustrated in Figure 1. 

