#### 2.6.1. Respiratory Muscle Training

Respiratory muscle training will be performed using a calibrated Expiratory Muscle Strength Trainer (EMST-150) and an inspiratory adapter (IA-150) (EMST 150; Aspire Products, Gainesville, FL, USA). 

In a previous in-person session, patients will be trained to use the device. They will be instructed to sit in a proper position in a chair, wear nose clips, take a deep breath, hold their cheeks lightly, blow as hard as they can into the device, and ensure that air flows freely through the device. Written instructions with pictures and text will also be provided to each patient.

The home-based respiratory training sessions will consist of two sets of 15 breaths (15 repetitions of inspiratory muscle training and 15 repetitions of expiratory muscle training) with 2 min of recovery between the sets. Training will be conducted twice daily, 5 days per week for 6 weeks, at the same time each day. Training loads will be set at a pressure equivalent to 30% of maximal inspiratory and expiratory pressures and will be increased weekly at intervals of 10 cmH_2_O [35,36]. This resistance will be readjusted if needed according to the patient’s tolerance. The number of repetitions will also increase starting from the third week to a maximum of 5 sets of each inspiratory and expiratory exercise per day, as tolerated. Patients will complete a diary indicating the number of repetitions per day and the time of day. Additionally, patients will use a visual analog scale from 0 to 10 to rate their symptoms of fatigue, dizziness, or pain during the training, where 0 represents no symptoms and 10 represents maximal severity. Once per week, the patient will have a video call from the therapist to review the diary and any symptoms that appeared during training, adjust the progression, and resolve any doubts. Adherence will be assessed using this diary. 

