A study conducted by Krekeler et al. [17] observed that the dosage and intensity in clinical practice are lower compared to research studies. In our study, the respiratory muscle training devices are relatively inexpensive, portable, and easy to use. They require no specialist assistance, making them suitable for use in a home environment. A previous trial focused on supervised, home-based respiratory muscle training showed positive results, achieving a significant improvement in the quality of life of the participants [56]. Our study seeks to increase accessibility to therapy and improve the benefits of the standard intervention by increasing the dosage. Treatment adherence is an important but still unresolved health issue, especially in interventions involving home-based exercises [57]. Increased compliance is linked to an increase in cost-effectiveness. Several systematic reviews have reported that diaries are one of the most used tools to measure adherence in home-based approaches [58,59]. In our study, the patients will complete a diary indicating the repetitions and the symptoms associated with exercise performance.

The proposed home-based respiratory training ensures an individualized program with the appropriate intensity and duration, adapted to the symptoms and baseline values of each participant. Adherence will be facilitated through regular monitoring and program adjustments based on patient progress and feedback. Additionally, the home-based respiratory training will be integrated with other therapeutic interventions for dysphagia, such as dietary modifications, postural adjustments, and traditional swallowing exercises, to achieve comprehensive rehabilitation.

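### The only analysis population stated drops randomised participants for low adherence, and the adherence measure includes a diary that the control arm does not have

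*Protocol article*

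**What the plan says.** Section 2.9 (Statistical Analysis) closes with this rule: "Participants with adherence rates of 80% or less, based on home diaries and attendance to standard speech and language sessions, will be excluded". The exclusion applies to the analysis as a whole. Nothing in the article confines it to a per-protocol or sensitivity set, and no analysis of all randomised participants is mentioned.

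The diary is introduced only in section 2.6.1, on respiratory muscle training: "Patients will complete a diary indicating the number of repetitions per day and the time of day", and then "Adherence will be assessed using this diary". Section 2.6 gives the experimental arm a "6-week home-based respiratory muscle training program in addition to the standard speech and language intervention", whereas "Patients in the control group will receive only the standard intervention". Attendance at standard therapy is recorded in both arms (section 2.6.2).

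The sample size in section 2.8 is 55, "accounting for a 15% dropout rate". It mentions no allowance for adherence exclusions. The Discussion itself warns: "Treatment adherence is an important but still unresolved health issue, especially in interventions involving home-based exercises".

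**The concern.** Randomisation makes the two arms comparable at the start. Removing people for what they do afterwards can undo that, particularly when the assigned treatment influences the behaviour. Here it can: home training adds a daily task, and section 2.6.1 expects some fatigue, dizziness or pain. Those symptoms could lower adherence in one arm only.

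A common criterion applied alike to both arms would still be a departure from the randomised comparison, but any selection would tend to be similar on each side. This criterion is not common to both arms, because one of its two components exists only in the experimental arm. At stake is whether a difference in PAS, respiratory pressures or cough flow can be attributed to the training rather than to who was left in the analysis. If outcomes are not collected from non-adherent participants, the problem cannot be repaired later.

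**Working it through.** **1. The plan's own sample size.** Inputs from section 2.8: difference 1 PAS point, SD 1.2, power 80%, alpha read as 0.05 two-sided, dropout 15%.

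n per arm = 2 × 1.2² × (1.960 + 0.842)² / 1² = 22.6, rounded up to 23, so 46 in total. 46 / 0.85 = 54.1, rounded up to 55. The stated 55 is reproduced. The inflation is fully used by the 15% dropout.

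**2. What the rule demands of each arm.**
- Standard therapy, both arms: 3 × 6 = 18 sessions. 14/18 = 77.8% is excluded and 15/18 = 83.3% is kept.
- Home training, experimental arm only: 2 × 5 × 6 = 60 sessions. Counted by session, 48/60 = 80.0% is excluded and 49/60 is kept.

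The text does not say whether the two components are separate thresholds or one combined rate.
- *Separate thresholds:* experimental patients must pass both and controls one. If 85% pass each and the two are independent (assumptions), 0.85 × 0.85 = 72% of the experimental arm and 85% of controls are kept.
- *One combined rate, pooled by session:* 60 of 60 + 18 = 78 experimental sessions, or 77%, come from the diary. Someone who misses 4 therapy sessions but reports full home training scores 74/78 = 94.9% and stays. A control who misses the same 4 scores 77.8% and is removed.

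The rule is unequal under both readings, although not in the same way.

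**3. Bias if training does nothing.** The documents give no adherence rate and no adherence-outcome correlation, so both are assumed. Let adherence be standard normal, correlated r with a better (lower) PAS, SD 1.2. If the most adherent fraction k is kept, mean adherence among those kept is φ(c)/k, where c is the cut-off.

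φ(c)/k is 0.274 for k = 85%, 0.468 for 72% and 0.644 for 60%.

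Spurious benefit = 1.2 × r × (experimental value − control value). Type I error is from simulation with 23 per arm before exclusion and a two-sided t-test at 0.05.

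| Kept, experimental vs control | r | Spurious PAS benefit | Type I error |
|---|---|---|---|
| 72% vs 85% | 0.3 | 1.2 × 0.3 × 0.193 = 0.07 | 5.3% |
| 72% vs 85% | 0.5 | 1.2 × 0.5 × 0.193 = 0.12 | 5.9% |
| 60% vs 85% | 0.3 | 1.2 × 0.3 × 0.370 = 0.13 | 6.1% |
| 60% vs 85% | 0.5 | 1.2 × 0.5 × 0.370 = 0.22 | 8.3% |
| either | 0 | 0 | 5% |

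With half the experimental arm removed and r = 0.5, type I error is about 11%. With equal retention on the same criterion the bias is about zero.

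**4. Analysed numbers.** 55 / 2 = 27.5 per arm, and 27.5 × 0.85 = 23.4 after dropout, which gives about 80% power by the t-test. For 72% vs 85% kept:
- No overlap between exclusions and dropout: 23.4 × 0.72 = 16.8 and 23.4 × 0.85 = 19.9, power about 69%.
- All dropouts already among those excluded: 27.5 × 0.72 = 19.8 and 27.5 × 0.85 = 23.4, power about 76%.

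**The case against.** **The direction of bias is not in the documents.** A reader might infer that the rule must favour training. The text does not support that. Section 2.6.1 lets resistance and repetitions follow tolerance, with a weekly call to adjust them, which could protect weaker patients from counting as non-adherent. The combined-rate reading could even keep experimental patients whose attendance would exclude a control. This stands: the direction depends on who is removed and how they fare.

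**Two separate hurdles are only one reading.** This also stands, as does the point that the diary records repetitions, whose target changes from week 3, so the count of 49 out of 60 is itself an interpretation. The inequality survives, because controls have no diary under either reading.

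**Loss of power is not a secure complaint.** A reader might infer that the planned 80% is simply lost. That depends on overlap with dropout, which section 2.8 does not define, and on holding the effect at 1 point in every population. If the 28% who are non-adherent get half the benefit (assumption), the effect in all randomised patients is 0.72 × 1 + 0.28 × 0.5 = 0.86, and power with 23.4 per arm is about 67%. Analysing everyone therefore does not necessarily give more power. What remains is that the 15% is described as dropout only.

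**The rule may fit the stated question.** A reader might infer that the trial asks about the effect of offering training, and that the rule answers something else. The article does not use that wording; its hypothesis concerns patients who receive training. The case against the rule rests on the loss of the randomised comparison, not on a mismatch with the objective.

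**An analysis plan might add a full analysis.** It might, but the article does not leave the matter open. It states who "will be excluded from the statistical analysis", and a plan that follows it carries the rule forward.

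**Conclusion.** The point holds. The article's only stated analysis population is selected on a post-randomisation behaviour, measured with a component that exists in one arm only. That follows from sections 2.6, 2.6.1 and 2.9 without any assumption.

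The size is conditional. With 60% to 72% versus 85% kept and a correlation of 0.3 to 0.5, the spurious benefit is about 0.07 to 0.22 PAS points against a target of 1 point, and type I error is just over 5% to about 8%. Retention, independence and correlation are all assumed, and with no correlation the bias is about zero. Analysed numbers may fall below plan to the extent that adherence exclusions do not overlap with dropout. The documents do not settle by how much.

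**What to change.** Replace the last sentence of section 2.9 with wording such as:

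> The primary analysis includes all randomised participants in the arm to which they were assigned, regardless of adherence. Participants are asked to attend the post-intervention assessment even if they stop training. Missing outcomes are handled by a pre-specified method.

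State that method; one option is a baseline-adjusted model, with multiple imputation as a sensitivity analysis. Keep the >80% set as a labelled per-protocol sensitivity analysis, say whether diary and attendance are separate thresholds or one rate, define the diary denominator, and report adherence by arm.

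The cost is wording, plus inviting non-adherent participants to an assessment that Table 1 already schedules. The downside is that the estimated effect may be smaller than among full adherers. The change should be made while outcomes can still be collected from participants who stop training.
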